### Sample size

To calculate the adequate sample size, the expert group set the difference of primary outcome measure between the two groups to 10 mm with the standard deviation of 13.66 on the basis of a previous similar study [32]. With 1:1 ratio, 80% power, and a 0.05 significance level for the independent t-test, we calculated the sample size using the formula below (α = 0.05, β = 0.2, σ = 0.3.66 and *d* = 10):$$ \mathrm{n}=2{\sigma}^2{\left({\mathrm{Z}}_{\alpha /2}+{\mathrm{Z}}_{\beta}\right)}^2/{d}^2 $$

Considering a 10% dropout rate and 95% compliance to the calculated value, we determined that adequate sample size in each group is 35 participants. The 70 participants will be recruited separately at the four research sites; each site will recruit the following numbers of participants: KHUHGD, 18; KHUMC, 18; DUBOH, 18; DKMHDHU, 16.

### Randomization and allocation concealment

At each institution, the 70 participants will be randomly allocated to the TEA group or STEA group according to a randomization procedure with a 1:1 ratio. The randomization sequence will be generated by an independent statistician using the randomization program of the statistical analysis system. Next, sealed, opaque envelopes containing random code will be sent to each institution. The CRC will open the envelope and allocate participants to their groups. To conceal the allocation until the end of the study, information about the allocation will be recorded in a separate log and provided only to those researchers who are carrying out the intervention.

### Blinding

To achieve patient–assessor blinding, only the CRC will handle the allocation information. The CRC will provide restricted information in accordance with the researchers’ role in the study. We will explain to the participants only that they will be treated using one of the two interventions: TEA or STEA. Each participant will be treated at a different time to prevent an exchange of information. The participants in each group will receive treatment at the same sites and they will be placed in a prone position so that they cannot see the procedure. Practitioners will minimize their conversation with the participants. The researchers conducting the assessment will be blinded to the allocation, and they will only ask about what is essential to complete the case report form (CRF). An independent statistician will analyze the research data and will not be given information about the allocation.

### Statistical methods

The data will be corrected using the “last observation carried forward” method and then analyzed using the “intention-to-treat” principle. The independent t-test and Chi-square test will be used to compare differences in general characteristics between the groups. As a primary outcome, changes in the 100-mm VAS for lower back pain from baseline to the end of the eighth treatment will be compared between the groups using the independent t-test. To compare the outcomes at each session with the baseline values, an analysis of covariance will be used. Trends over time and time-by-treatment interactions will be analyzed using a repeated measures analysis of variance. All statistical analyses will be performed using PASW statistics 18 for Windows, and the statistical significance level will be considered to be 0.05 (two-sided), with 95% confidence intervals.

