### Primary outcome measure

The intensity of lower back pain will be evaluated using the 100-mm VAS [25]. At pre-trial screening, at weeks 1 (baseline), 4, and 8 (primary endpoint), and at weeks 12 and 16 (follow-up sessions), participants will be asked to record their pain intensity within the past week on a 100-mm linear scale (0, absence of pain; 100, worst pain imaginable). Change from baseline after eight sessions of treatment will be compared between the groups as the primary outcome.

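### Last observation carried forward is the only stated missing-data rule for the week-8 primary test; it can bias the treatment difference in either direction and takes power below 80% at the planned dropout

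*Protocol article*

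**What the plan says.** The Statistical methods section opens with the missing-data rule: "The data will be corrected using the “last observation carried forward” method and then analyzed using the “intention-to-treat” principle". It sets no limit by outcome or visit. The primary analysis follows in the same paragraph: "changes in the 100-mm VAS for lower back pain from baseline to the end of the eighth treatment will be compared between the groups", by independent t-test. The longitudinal analysis comes after it: "Trends over time and time-by-treatment interactions will be analyzed using a repeated measures analysis of variance". No second missing-data method is named.

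The Primary outcome measure section sets the lower back pain VAS at screening and then "at weeks 1 (baseline), 4, and 8 (primary endpoint), and at weeks 12 and 16 (follow-up sessions"). Baseline and week 4 are therefore the only post-enrolment values that can be carried to week 8.

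The Sample size section expects missing data: "Considering a 10% dropout rate and 95% compliance to the calculated value, we determined that adequate sample size in each group is 35 participants".

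**The concern.** LOCF gives the right week-8 value only if a patient's pain stops changing on the day of dropout. This trial measures change over eight weekly sessions, so that is hard to assume. A patient lost before week 4 enters the t-test with a change of exactly zero. A patient lost between weeks 4 and 8 enters with a mid-treatment value. Both count as measurements.

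Two consequences follow. If TEA works and its advantage grows with time, dropouts dilute the estimate even when both arms lose the same share. If one arm loses more patients, or loses them earlier, that imbalance becomes a treatment difference whether or not TEA works. The primary estimate is exposed to both.

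This is not a gap that an unseen analysis plan might fill. The article positively chooses the method, and a plan that follows the article inherits it.

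**Working it through.** **Plan's own figure.** Inputs from Sample size: "the difference of primary outcome measure between the two groups to 10 mm with the standard deviation of 13.66"; "With 1:1 ratio, 80% power, and a 0.05 significance level for the independent t-test". The test is two-sided.

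n = 2 × 13.66² × (1.960 + 0.842)² / 10² = 29.29 per arm. Then 29.29 / 0.90 / 0.95 = 34.26, rounded up to 35, which matches. (The SD is misprinted once in that section; 13.66 is the value that gives 35.) The 10% allowance treats dropouts as lost: 35 × 0.90 = 31.5 per arm remain. LOCF puts them back with a zero or partial change.

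**Assumptions not in the documents.** SD of change 13.66 at weeks 4 and 8; correlation 0.6; half of the week-8 fall reached by week 4; dropout independent of outcome within arm. Dropout is placed wholly before or wholly after week 4 to give the range.

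**Formulas.** Let F be an arm's mean fall at week 8, d its dropout share and s² = 13.66² = 186.6.

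- Lost before week 4: LOCF mean (1 − d)F; variance (1 − d)s² + d(1 − d)F².
- Lost after week 4: LOCF mean (1 − d)F + dF/2; variance s² + d(1 − d)(F/2)².
- SE = √[(variance sham + variance TEA) / 35].

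**A. True effect 10 mm (falls 20 v 30 mm), equal 10% dropout.**

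- Before week 4: difference 0.9 × 30 − 0.9 × 20 = 9.0 mm. Variances 167.9 + 36.0 = 203.9 and 167.9 + 81.0 = 248.9; SE = √(452.8 / 35) = 3.60. Normal approximation to power: Φ(9.0/3.60 − 1.96) = 0.71; simulated t-test 0.69.
- After week 4: difference (27 + 1.5) − (18 + 1) = 9.5 mm. Variances 195.6 and 206.9; SE 3.39. Approximation Φ(9.5/3.39 − 1.96) = 0.80; simulated t-test 0.79.
- Observed week-8 values only: difference 10.0 mm; SE = 13.66 × √(2/31.5) = 3.44. Approximation 0.83; simulated t-test 0.81.

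**B. True effect 10 mm, unequal dropout.**

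- TEA 15%, sham 5%: 0.85 × 30 − 0.95 × 20 = 6.5 mm (before week 4); 27.75 − 19.5 = 8.25 mm (after).
- TEA 5%, sham 15%: 0.95 × 30 − 0.85 × 20 = 11.5 mm (before); 29.25 − 18.5 = 10.75 mm (after).

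**C. No true effect, both arms fall by F.** The spurious difference is the gap in dropout times the shortfall, which is F before week 4 and F/2 after it. Type I error is from simulation of the t-test.

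| Dropout | F | Lost before week 4 | Lost after week 4 |
|---|---|---|---|
| 10% v 10% | 20 to 30 mm | 0 mm; about 5% | 0 mm; about 5% |
| 15% v 5% | 20 mm | 2.0 mm; 9% | 1.0 mm; 6% |
| 15% v 5% | 30 mm | 3.0 mm; 12% | 1.5 mm; 7% |

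Hand check of the largest case (F = 30 mm, before week 4): variances 177.3 + 42.8 = 220.1 and 158.6 + 114.8 = 273.4; SE = √(493.5 / 35) = 3.75; Φ(3.0/3.75 − 1.96) + Φ(−3.0/3.75 − 1.96) = 0.13. On observed data, type I error was near 5% in every null case.

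**The case against.** The strongest reply is that the damage depends on things the article does not say. It states one 10% dropout rate, with no difference between arms. Patients and assessors are blinded, and everything except the thread is the same in both groups, so a threefold gap in dropout (about 5 v 2 of 35 patients) need not occur. A smaller gap does less: at 12.5% v 7.5%, type I error is about 6% to 7% for dropout before week 4 and little above 5% after it. A smaller fall also does less: 10 mm in both arms with 15% v 5% gives 1 mm and about 6%. The falls of 20 to 30 mm and the correlation are assumptions. All of this stands, and it limits what can be claimed about type I error.

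It does not rescue the rule. In the one dropout scenario the plan states, with no imbalance, LOCF still lowers the estimate and the power under the assumed trajectories.

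Two stronger readings are tempting.

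- A reader might infer that the primary p-value and confidence interval are invalid as such. The calculations do not support that: with equal dropout and no effect the test keeps its 5% level, chance imbalance included. A systematic difference in amount, timing or reason is needed.
- A reader might also fault the repeated-measures ANOVA for assuming sphericity with uneven visits. The gaps are 3, 4, 4 and 4 weeks, sphericity does not require even spacing, and corrections for it are commonly left to an analysis plan. What remains is that this secondary analysis would run on LOCF-filled values; its error was not simulated.

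**Conclusion.** The concern holds as a risk of bias on the primary endpoint, moderate in size. At the planned 10% dropout, equal in both arms, the loss is about 0.5 to 1 mm of a 10 mm effect, and power falls below the stated 80%. With systematic imbalance of 15% v 5%, the error is about 1 to 3 mm under the null; with a true effect, the estimate can fall to 6.5 mm or rise to 11.5 mm. LOCF therefore cannot be defended as conservative.

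These sizes rest on the assumed trajectories, correlation and dropout patterns. The core does not: a stated rule scores expected dropouts at zero or mid-treatment change and treats those scores as data. It should be fixed, but the documents do not show that the primary result would be unusable without the change. The sample size of 35 per arm is correctly derived and is not in question.

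**What to change.** For the primary analysis, replace LOCF and the t-test with one likelihood-based mixed model for repeated measures on the VAS visits already scheduled (weeks 4, 8, 12 and 16), with the week-8 treatment contrast as primary. Keep patients who have only a baseline value, by a constrained-baseline model or by multiple imputation by arm, so that the intention-to-treat set stays whole. Use the same model for the time-by-treatment question in place of ANOVA on LOCF-filled data. Keep LOCF only as a sensitivity analysis, beside a delta-adjusted one.

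Under the dropout mechanism assumed above, a t-test on observed week-8 data would already remove the bias. The model is preferred because it also covers dropout that depends on scores already observed; it was not itself simulated here.

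Document the change before unblinding. The Blinding section says the statistician is not told the allocation, so this can be done credibly. The cost is revised wording and slightly more analysis work, with no new data.

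### The primary t-test on change leaves out baseline VAS and site, which usually costs precision, and the ANCOVA sentence describes a visit-versus-baseline comparison that ANCOVA does not make

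*Protocol article*

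**What the plan says.** All references are to the protocol article.

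- **Primary analysis (Statistical methods).** The change in low back pain VAS from baseline to the end of the eighth treatment "will be compared between the groups using the independent t-test". No covariate and no site term is named. Missing values are filled by last observation carried forward, and the analysis follows intention to treat.
- **ANCOVA (same section).** "To compare the outcomes at each session with the baseline values, an analysis of covariance will be used". No covariate and no contrast between arms is stated.
- **Longitudinal analysis (same section).** A repeated measures ANOVA examines trends and the interaction of treatment with time.
- **Randomization and allocation concealment.** "At each institution, the 70 participants will be randomly allocated to the TEA group or STEA group", in a 1:1 ratio. The site quotas are 18, 18, 18 and 16. The article does not use the word stratified.
- **Sample size.** The expert group "set the difference of primary outcome measure between the two groups to 10 mm with the standard deviation of 13.66". The calculation is done "With 1:1 ratio, 80% power, and a 0.05 significance level for the independent t-test" and then allows for dropout and compliance.
- **Participants and Table 2.** Entry requires a low back pain VAS of at least 40 mm. VAS is recorded at screening and at baseline. The global perceived effect (GPE) has no baseline assessment.

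**The concern.** The baseline value usually predicts the week-8 value, and it is already collected. A t-test on change gives baseline a fixed coefficient of one, whereas ANCOVA estimates the coefficient from the data. When the true coefficient is below one, the change score over-corrects, and a chance difference in baseline between two arms of about 35 carries into the estimate through regression to the mean. The sample size leaves little margin above 80% power, so lost precision matters here.

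The ANCOVA sentence raises a different problem. Comparing each visit with baseline is a contrast over time within patients. ANCOVA does not perform that contrast; it compares groups on a later value, given the baseline value. Both arms receive the same needling at 23 points, so both may improve, and improvement from baseline would say nothing about the effect of the thread. Read literally, the sentence also cannot be carried out for GPE.

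**Working it through.** **Inputs from Sample size and Statistical methods.** Difference 10 mm; SD 13.66 mm (the article does not say whether this is the SD of change or of a single score); two-sided α 0.05; power 80%; 10% dropout; 95% compliance; 35 per arm.

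**Inputs assumed, because the article does not give them.** Correlation ρ between baseline and week-8 VAS: 0.3, 0.5, 0.7. Ratio k of baseline SD to week-8 SD: 1, 0.8, 0.7, 0.6. Share of variance explained by site: 2%, 5%, 10%.

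**1. The plan's own figure.** n = 2 × 13.66² × (1.960 + 0.842)² / 10² = 29.29 per arm. Inflated: 29.29 / (0.90 × 0.95) = 29.29 / 0.855 = 34.26, rounded up to 35. The stated 35 per group reproduces. (The σ printed beside the formula is a misprint; 13.66 is the value that gives 35.)

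**2. Power of the planned t-test.** Evaluable per arm: 35 × 0.90 × 0.95 = 29.9. With the noncentral t distribution, power is 79.5%. If carrying observations forward keeps all 35 per arm in the analysis and nothing is diluted, it is 85.5%.

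**3. Power with baseline adjustment.** Take 13.66 as the SD of change. With σ the week-8 SD:

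- variance of change = σ²(1 + k² − 2ρk)
- residual variance of ANCOVA = σ²(1 − ρ²)
- ratio = (1 − ρ²) / (1 + k² − 2ρk), which is (1 + ρ)/2 when k = 1
- ANCOVA residual SD = 13.66 × √ratio

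Variance ratio and ANCOVA power at 29.9 per arm (t-test: 79.5%):

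| k | ρ = 0.3 | ρ = 0.5 | ρ = 0.7 |
|---|---|---|---|
| 1 (equal variances) | 0.65; 93.2% | 0.75; 89.5% | 0.85; 85.5% |
| 0.8 | 0.78; 88.2% | 0.89; 83.8% | 0.98; 80.3% |
| 0.7 | 0.85; 85.5% | 0.95; 81.5% | 1.00; 79.5% |
| 0.6 | 0.91; 83.1% | 0.99; 80.0% | 0.98; 80.3% |

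The rows below k = 1 matter because a floor of 40 mm at entry tends to narrow the spread at baseline but not at week 8. When ρ = k there is no gain. The degree of freedom spent on the covariate changes these powers by less than 0.1 point.

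**4. If 13.66 were instead the SD of a single score** (equal variances, 30 per arm, normal approximation). The SD of change is 13.66 × √(2(1 − ρ)). The t-test on change would have about 67% power at ρ = 0.3 and 81% at ρ = 0.5, against 84% and 91% for ANCOVA.

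**5. Site.** If site explains a share f of the variance and the arms are balanced within site, the residual SD is 13.66 × √(1 − f). Power at 29.9 per arm rises from 79.5% to about 80.3%, 81.5% and 83.5% for f = 2%, 5% and 10%. Leaving site out is conservative: the actual two-sided error rate would be about 4.8%, 4.4% and 3.9% instead of 5%.

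**6. The ANCOVA sentence beside its neighbour.** The ANCOVA sentence names visits and baseline but no arms. The sentence after it names the interaction of treatment with time, which is a comparison between arms over the course of the trial. The defect therefore lies in one sentence.

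**The case against.** The strongest reply is that the primary analysis is coherent. The outcome definition, the sample size and the analysis section agree on change from baseline compared by a t-test. Under randomisation that test is unbiased, and a chance baseline difference is sampling error, not bias. All of this stands. A reader might infer that the primary test is invalid or that the trial is wrongly sized; the article supports neither.

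The second reply is that the gain cannot be derived from the article, which gives no correlation, no ratio of SDs and no statement of what 13.66 measures. This also stands. The 86% to 93% range should not be read as the gain for this trial, since under a narrowed baseline spread most of it can vanish.

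Third, a reader might infer that the secondary analyses as a whole fail to compare the arms. They do not fail as a whole: the interaction in the repeated measures ANOVA compares them. The ANCOVA sentence may itself be loose wording for a baseline-adjusted comparison between arms, in which case rewording settles it.

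Fourth, allocation at each institution suggests stratification by site but does not state it, so the case for a site term is weaker than the case for baseline.

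One might add that an article leaves covariates to the full protocol or the SAP. That does not remove the point: the article names the primary test, and an adjusted analysis elsewhere would contradict it.

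**Conclusion.** The point holds as a matter of efficiency and clarity, not of validity. With 13.66 mm as the SD of change and 29.9 evaluable per arm, replacing the t-test by ANCOVA adds between nothing and about 14 points of power (93.2 − 79.5 = 13.7) over the assumed ranges of ρ and k. The upper end needs equal variances and a correlation of 0.3. Apart from one degree of freedom, ANCOVA is no less precise in any of these scenarios, and it also corrects for chance baseline imbalance. Site adjustment probably adds about 1 to 4 points, if site explains 2% to 10% of the variance and allocation is balanced within site.

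The ANCOVA sentence needs correcting whatever these quantities are, because it assigns the method to a comparison that it does not make and names no contrast between TEA and STEA. The change is worth making because it is nearly free.

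**What to change.** 1. Make the primary analysis an ANCOVA of week-8 low back pain VAS (or of change, which gives the same treatment effect) on treatment, baseline VAS and site. Report the adjusted TEA minus STEA difference with its 95% CI. Keep the unadjusted t-test as a sensitivity analysis; the sample size can stay as it is.
2. Reword the ANCOVA sentence as a comparison between arms at each visit, with the baseline value and site as covariates, for outcomes that have a baseline.
3. For GPE, state a comparison between arms without a baseline covariate.
4. State whether randomisation is stratified by site and whether 13.66 is the SD of change.

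The cost is wording in the analysis section, with no new data, visits or patients. Because the Trial status section gives an estimated completion date of 30 June 2018, the change should be dated and recorded before the allocation is unblinded for analysis.

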### Data collection and management

The following data will be collected and cross-checked by two independent researchers using the CRF: characteristics of participants; outcomes; and AEs. All data and documents obtained during the study period will be confidentially managed according to the standard operation protocol (SOP) of the IRBs. No private data unrelated to the study will be collected and personally identifiable information will be discarded after a certain period, in accordance with the SOP. The researchers will be given training in protecting the privacy of participants.

### Safety

At the pre-trial screening, the following tests will be performed: complete blood count; liver and renal function tests; blood coagulation test; urinalysis; and pregnancy test (if necessary). Information about expected AEs, as well as a contact number, will be given to the participants along with the informed consent form before the pre-trial screening. If AEs do occur, the principal investigator will evaluate the severity of the incident, as well as its relation to the interventions. They will then provide proper examination and treatment in accordance with the compensation rules. Particularly, in the case of serious AEs, the participants will be removed from the study. The progress of all AEs will be recorded in the CRF and handled in accordance with the regulation of KGCP.

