3. Treatment regimen	3a. Number of treatment sessions: Eight
	3b. Frequency and duration of treatment sessions: Once a week for 8 weeks
4. Other components of treatment	4a. Details of other interventions administered to the acupuncture group: Rescue medication, lifestyle, education
	4b. Setting and context of treatment, including instructions to practitioners, and information and explanations to patients: Minimized conversation between practitioner and participant
5. Practitioner background	5. Description of participating acupuncturists: Specialists from the acupuncture and moxibustion department or residents supervised by a specialist with at least 3 years of clinical experience
6. Control or comparator interventions	6a. Rationale for the control or comparator in the context of the research question, with sources that justify this choice: Thread-removed TEA will be used as a comparator. In this way, the study focuses specifically on the existence of thread.
	6b. Precise description of the control or comparator. If sham acupuncture or any other type of acupuncture-like control is used (provide details as for Items 1 to 3 above): All conditions other than the use of thread-removed TEA will be the same as those in the treatment group.

*STRICTA* Standards for Reporting Interventions in Clinical Trials of Acupuncture, *TEA* thread-embedding acupuncture

The selection of acupoints and details of the procedure have been modified from similar studies [21–24] by a committee of Korean medicine doctors (KMDs) experienced in LHIVD and TEA. All therapeutic procedures will be performed by KMDs who have completed or have been taking a specialist acupuncture and moxibustion course for at least three years. To ensure homogeneity of intervention among the participating centers, all practitioners will undertake a training course together in advance.

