### Outcomes

The primary outcome will be change in the intensity of lower back pain. The secondary outcomes will be intensity of radiating pain, functions of daily life, QoL, and global perceived effect (GPE). Additionally, all AEs will be recorded at each visit and assessment of blinding will be conducted at the end of the study. All assessments will be performed by independent researchers who are not involved in the scheduled intervention (Table 2).

**Table 2 Tab2:** Schedule for assessment

Outcome measures	Screening	Baseline	Treatment (weeks 1–8)		Follow-up (weeks 9–16)	
			Week 4	Week 8	Week 12	Week 16
VAS for lower back pain	◎	◎	◎	◎	◎	◎
VAS for radiating pain		◎	◎	◎	◎	◎
ODI		◎	◎	◎	◎	◎
RMDQ		◎	◎	◎	◎	◎
EQ-5D-5 L		◎	◎	◎	◎	◎
GPE			◎	◎	◎	◎
Assessment of binding						◎
Adverse events^a^		◎	◎	◎	◎	◎

^a^Adverse event will be monitored throughout the study period

*VAS* visual analogue scale, *ODI* Oswestry Disability Index, *RMDQ* Roland-Morris disability questionnaire, *EQ-5D-5 L* EuroQol 5 Dimensions 5 Levels, *GPE* global perceived effect

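### A serious adverse event takes the participant out of the whole study, not just off treatment, creating avoidable and possibly informative gaps that LOCF must fill

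*Protocol article*

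**What the plan says.** The rule is in the Safety section of the protocol article: "Particularly, in the case of serious AEs, the participants will be removed from the study". Just before it, the principal investigator is asked to judge how severe the event is and whether it is related to the intervention, but the removal rule does not depend on either judgement. The only data collection described afterwards concerns the event itself: "The progress of all AEs will be recorded in the CRF and handled in accordance with the regulation of KGCP". The footnote to Table 2 (Outcomes) adds: "Adverse event will be monitored throughout the study period". Nothing says that the VAS, ODI, RMDQ, EQ-5D-5L or GPE assessments go on after removal.

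Missing data are handled in one sentence under Statistical methods: "The data will be corrected using the “last observation carried forward” method and then analyzed using the “intention-to-treat” principle". The primary comparison is defined under Primary outcome measure: "Change from baseline after eight sessions of treatment will be compared between the groups as the primary outcome". Low back pain VAS is scheduled at screening, baseline and weeks 4, 8, 12 and 16.

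**The concern.** Stopping treatment and leaving the study are different things. Participant safety may require the first. It does not require that outcome measurement stop, yet the sentence imposes both for every serious adverse event, including one unrelated to the needling or the thread.

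The event occurs after randomisation and may depend on the arm. Table 1 (item 6a) says of the sham comparator: "In this way, the study focuses specifically on the existence of thread". A serious event caused by the thread would therefore fall in one arm only. A serious event could also be a worsening of the disc disease, which bears directly on the pain outcome. In either case the missing values could be informative. LOCF replaces them with a value recorded before the event, so any effect of the event on pain is left out of the comparison.

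This is not a formal contradiction of intention-to-treat, because a removed participant can still be analysed in the randomised arm. What is at stake is that the intention-to-treat estimate then rests, for these participants, on imputed values where observed ones could have been collected.

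**Working it through.** **1. What LOCF puts in, by time of removal** (schedule from Table 2 and Primary outcome measure)

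| Removal | Week 8 VAS used | Change entering the primary t-test |
|---|---|---|
| Before week 4 | Baseline | 0 |
| Between weeks 4 and 8 | Week 4 | Change to week 4 only |
| After the week 8 assessment | Observed | Unaffected; weeks 12 and 16 are imputed |

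GPE has no baseline measurement, so for a removal before week 4 there is no earlier GPE value to carry forward.

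**2. The plan's own figure** (inputs from Sample size: difference 10 mm, SD 13.66 mm, 80% power, 0.05; two-sided per Statistical methods)

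n = 2 × 13.66² × (1.960 + 0.842)² / 10² = 29.29 per group. Allowing for 10% dropout and 95% compliance: 29.29 / (0.90 × 0.95) = 34.26, rounded up to 35. The stated 35 per group reproduces, and this point does not dispute it.

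**3. Standard error of the group difference**

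SE = 13.66 × √(2/35) = 3.27 mm.

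**4. Shift in the group difference**

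If k of the 35 participants in one arm are removed before week 4, and each would have shown a week 8 change of g mm that LOCF records as zero, the arm mean moves by k × g / 35. Both k and g are assumptions.

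| k (share of arm) | g = 10 mm | g = 20 mm | g = 30 mm |
|---|---|---|---|
| 1 (2.9%) | 0.29 | 0.57 | 0.86 |
| 2 (5.7%) | 0.57 | 1.14 | 1.71 |
| 3 (8.6%) | 0.86 | 1.71 | 2.57 |

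The range of 0.29 to 2.57 mm is 3% to 26% of the 10 mm target and 0.29/3.27 = 0.09 to 2.57/3.27 = 0.79 of the standard error. If the removed participants had stayed in assessment, this component would be zero.

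**5. Direction**

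For removals in the TEA arm, LOCF works against TEA if the participants would have improved, and in its favour if they would have worsened. In the STEA arm the reverse holds. The sign cannot be fixed in advance.

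**6. How likely any removal is**

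The article gives no serious adverse event rate. Taking 0.5% to 5% as an assumed range, with 70 participants and P(at least one) = 1 − (1 − p)^70:

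| Assumed rate p | Expected removals (70p) | P(at least one) |
|---|---|---|
| 0.5% | 0.35 | 30% |
| 1% | 0.7 | 50% |
| 2% | 1.4 | 76% |
| 5% | 3.5 | 97% |

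These cover the whole study period. Only events before the week 8 assessment touch the primary endpoint.

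**The case against.** The strongest objection is that the harm is remote. The 2.57 mm figure needs three early removals in one arm, none offsetting in the other, each hiding 30 mm in the same direction. Suppose the 5% rate spans 16 weeks with uniform timing. The chance of an event before week 4 is then 0.05 × 4/16 = 0.0125 per participant, and the binomial chance of three or more among 35 is about 1% per arm. At a 1% rate, about 0.7 × 8/16 = 0.35 events would be expected before week 8 across both arms. A single early removal costs at most 0.86 mm, or 0.26 of a standard error. This stands, and it is why the point is rated as a cheap improvement and not as a threat to the trial.

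Dependence on arm is also only a possibility. Both arms receive the same 23 insertions weekly and the same rescue drug, and the exclusion criteria remove many high-risk patients. Events from needling, acetaminophen or background illness would be shared between arms. This too stands.

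Part of the numerical shift belongs to LOCF, which affects every dropout. But the removal rule adds missing values that need not exist. The 10% dropout allowance (3.5 per arm) protects power; it does not protect against bias.

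The article is condensed, and a fuller protocol might separate treatment discontinuation from study withdrawal. That would excuse silence. Here the text shown states a mandatory rule, and nothing else in it softens that rule.

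Finally, pain scores after a serious event may reflect hospital care or analgesics as well as the study treatment. That is a fair point about interpretation. Observed values still fit the declared intention-to-treat principle better than a carried-forward pre-event score.

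**Conclusion.** The concern holds. The article fixes removal from the study for any serious adverse event, keeps only the event itself under follow-up, and leaves LOCF to supply the outcomes. The resulting missing data are avoidable and may be informative.

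The likely size is small: about 0.3 to 0.9 mm for one early removal, and up to 2.6 mm in an unlikely one-sided case of three, with direction unknown. Removals after the week 8 assessment leave the primary endpoint untouched, and equal numbers with similar missed changes in both arms would largely cancel. These figures rest on assumed counts and assumed missed changes, because the document gives no serious adverse event rate. The rule has no evident benefit for the participant beyond what stopping treatment alone would give, so it is worth changing even though the expected harm is modest.

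**What to change.** Replace the sentence in Safety with wording to this effect: a serious adverse event may end study treatment at clinical discretion; the participant remains in the study for all remaining scheduled assessments to week 16 and for adverse event follow-up, unless consent is withdrawn. In Statistical methods, state that values observed after treatment discontinuation are analysed in the randomised arm, and that imputation is used only for values that are truly missing.

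The cost is one protocol sentence (as an amendment at the four review boards), a CRF field separating treatment discontinuation from study withdrawal, and a few retained visits. The sample size stays at 35 per group.

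The Trial status section gives an estimated completion date of 30 June 2018, before the article's publication. If follow-up had closed by then, the lost visits cannot be recovered. In that case, report removals for serious adverse events by arm and by timing relative to weeks 4 and 8, and show how the primary result moves over a plausible range of week 8 values for those participants.
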